1. Overweight (including obesity): to determine the effect of early versus late introduction of complementary feed on the BMI, according to the IOTF cut-off values at 1 year.
2. Eating behavior and tolerating complementary feeding: to determine if early introduction is correlated with less eating problems in comparison to introduction the late introduction, by using the Baby Eating Behaviour Questionnaire (BEBQ) and Child Feeding Questionnaire (CFQ).
  - a. Subgroup analysis will be performed to explore if children with respiratory problems after birth requiring intubation have more eating problems than children without respiratory problems requiring intubation
  - b. Subgroup analysis will be performed to study if the duration of a feeding tube after birth is correlated with eating problems
  - c. Subgroup analysis will be performed to study if gestational age is related to eating disorders.
3. Eating behavior and tolerating complementary feeding: to determine if term born infants (control group B) have less eating problems in comparison to preterm infants before the start of complementary feeding, by using the Baby Eating Behaviour Questionnaire (BEBQ)
4. Growth parameters (weight, length, head circumference, BMI, weight-for-age, length-for-age, head circumference-for-age): comparing the growth parameters of preterm infants with term infants before the start of complementary feeding, at 1 year and at 2 years
5. Taken into account the food diaries at 6 months, 9 months, 12 months and 24 months and the start of complementary feeding
6. Health Related Quality of life (HRQoL): to evaluate the difference in HRQoL between early versus late introduction of complementary feeding, by using The Infant Toddler Quality of Life (ITQoL) Questionnaire or Pediatric Quality of Life Inventory (PedsQL).
7. Ages and Stages Questionnaire (ASQ): to evaluate the difference in development between early versus late introduction of complementary feeding, by using the ASQ at the age of 1 and 2 years.
8. Allergy/Atopic: to evaluate if the incidence of allergies is different between early versus late introduction of complementary feeding, by using the SCORAD.
9. Microbiota: to evaluate if the microbiota change due to the introduction of complementary feeding

:

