### **8.3.6 Eating behavior – Extra in this study**

The Baby Eating Behaviour Questionnaire (BEBQ) will be measured before the start of complementary feeding (12 weeks or 17 weeks) in both preterm and term born children (control group B). This questionnaire will be sent to the parents via Castor edc and will be filled out digitally. The BEBQ is a parent-report measure of appetite during the milk-feeding phase of infancy. Four dimensions emerged, with 17 items tapping four distinct feeding traits and one item describing general appetite. 'Enjoyment of food' (4 items) related to the infant's perceived liking of milk and of feeding in general, 'food responsiveness' (6 items) evaluates how demanding the infant is with regard to being fed and his or her level of responsiveness to cues of milk and feeding, 'slowness in eating' (4 items) measures the speed with which an infant typically feeds, and 'satiety responsiveness' (3 items) assesses how easily the infant gets full during a feed. BEBQ has shown a good reliability, with a Cronbach's alpha between 0.73-0.81.

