### **8.3.7 Child Feeding Questionnaire (CFQ) – Extra in this study**

The Child Feeding Questionnaire (CFQ) will be measured at the age of 2 years. This questionnaire will be sent to the parents via Castor edc and will be filled out digitally. It is a self-report measure to assess parental beliefs, attitudes, and practices regarding child feeding, with a focus on obesity proneness in children. The current version of the CFQ contains seven factors that fall into two categories. The first category, risk factors and concerns, measures factors that may elicit parental control in feeding and contains: perceived Feeding Responsibility, Perceived Parent Overweight, Perceived Child Overweight, and Concern about Child Overweight. The second category, control in child feeding: attitudes and practices, measures parents' attitudes and behaviors regarding child feeding and contains: Restriction, Pressure To Eat, and Monitoring. The reliability of both parents and child version is good: the Cronbach's alpha is respectively >0.70 and 0.66-0.88.

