## 10. STATISTICAL ANALYSIS

Since the sample size was not archived, the data will be interpreted with caution. Data will be analyzed on an intention to treat basis. In addition, we will also perform a per protocol analysis, taking into account the attrition rate. In case of missing values we will use multiple imputation. For the per protocol analysis, the criteria for the start of complementary feeding will be 12-13 weeks for the early group and 16-17 weeks for the late group. A p-value of 5% will be regarded as statistically significant and results will be presented with 95% confidence intervals.

Categorical data will be presented in absolute numbers and percentages. If a metric variable is normally distributed results will be shown in mean and standard deviation (sd). If a metric variable is not normally distributed median will be used with the interquartile range.

Descriptive data on BMI will be compared with the most recent Dutch growth chart. For the primary study parameter, the prevalence of obesity, the percentage of patients that develop overweight by using the IOTF will be calculated and intervention group and control will be compared including prevalence ratios with 95% confidence intervals. Furthermore, BMI and BMI z-scores between the intervention and control group will be compared as continuous variables.

The results of the questionnaires (BEBQ, CFQ, ITQoL / PedsQL, ASQ) will be analysed according to the scoring tables attached to the questionnaires. Allergy will be scored by a SCORAD form and can be presented as continuous or categorical variable. All blood and faeces results will be analysed as continuous or categorical variable. The diary results will be analysed as a continuous variable.

For all sub-objectives (as formulated in chapter 2), the intervention group and control group will be compared to determine the effect of early versus late introduction of complementary food, using a independent t-test or nonparametric test. For subgroup analysis, i.e. for children with respiratory problems or tube feeding, logistic regression will be used.

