For control group B, the preterm infants will be compared with the term infants to determine the difference of growth parameters, BEBQ results and food diaries before the start of complementary feeding, at 1 year and at 2 years of age. Growth parameters and BEBQ will be presented as continuous parameters (mean and sd or median with interquartile range). The growth parameters will be compared with the most recent Dutch growth curves. For the analyses, a t-test or nonparametric test will be used.

To take into account repeated measurement on the infants (non)linear mixed models will be used with infant as random factor and treatment (intervention, control), time and

time\*treatment as fixed factors. Infant and hospital will be added as random intercept. Random slopes will be added for time dependent variables.

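### Section 10 prescribes logistic regression for the intubation and tube-feeding questions, but the eating outcomes are multi-item scores, no binary eating problem is defined, and dichotomising them loses information

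*Protocol*

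**What the plan says.** Sub-objective 2 in Protocol Section 2 concerns eating behaviour, measured with the BEBQ and the CFQ. Two of its sub-questions matter here:

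- 2a: "Subgroup analysis will be performed to explore if children with respiratory problems after birth requiring intubation have more eating problems" than children who were not intubated.
- 2b: "Subgroup analysis will be performed to study if the duration of a feeding tube after birth is correlated with eating problems".

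Section 10 fixes the method for both: "For subgroup analysis, i.e. for children with respiratory problems or tube feeding, logistic regression will be used".

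The instruments are described as scales. For the BEBQ, Section 8.3.6 says: "Four dimensions emerged, with 17 items tapping four distinct feeding traits and one item describing general appetite". For the CFQ, Section 8.3.7 says: "The current version of the CFQ contains seven factors that fall into two categories". Neither section gives a threshold or a category for an eating problem. Section 10 refers to the scoring tables that come with the questionnaires, which are not reproduced in the protocol.

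Section 10 also says that the arms will be compared on all sub-objectives with an independent t-test or a nonparametric test. In its paragraph on the term-born control group B it adds: "Growth parameters and BEBQ will be presented as continuous parameters".

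**The concern.** Ordinary logistic regression needs a yes/no outcome. The protocol supplies scores and no rule for turning them into yes or no. The analyst must therefore take a cut-off from outside the protocol or set one, and the answers to 2a and 2b would depend on it.

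There is a second cost, which stays even if a good cut-off exists. Cutting a score in two treats every child on the same side as identical, and the analysis then needs more children for the same power. Within one section, the same eating outcomes would be analysed as scores between arms and as a dichotomy for the two exposure questions, with no reason given.

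**Working it through.** **1. Does another reading make the method fit?** Logistic regression would need no cut-off if intubation (yes/no) were the dependent variable and the eating score the predictor. That reverses 2a, which asks about eating problems given intubation. It does not work for 2b, where the exposure is a duration and the question is put as a correlation. The eating outcome is therefore the natural dependent variable in both.

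**2. The plan's own figure.** The protocol gives no sample size or power for 2a or 2b. The primary calculation in Section 4.3 serves only as a yardstick for the number of children. With 6% versus 13%, two-sided 5%, 80% power and pooled variance (mean rate 0.095):

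n = [1.96 × √(2 × 0.095 × 0.905) + 0.842 × √(0.06 × 0.94 + 0.13 × 0.87)]² / 0.07² ≈ 274.3, so 275 per group.

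That is 550 evaluable children, and 550 / 0.95 = 579 to be included. Both figures agree with the protocol.

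**3. Efficiency of a dichotomised score.** Assume a roughly normal score, with a fraction q of children classed as having problems, and let c be the matching cut-off on the standard normal scale. For small differences, the efficiency relative to analysing the score is φ(c)² / [q(1 − q)].

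| Classed as having problems | c | φ(c) | Efficiency | Children needed, relative to the score |
|---|---|---|---|---|
| 50% (median cut) | 0 | 0.399 | 0.159 / 0.25 = 0.64 | 1.57 times |
| 25% | 0.674 | 0.318 | 0.101 / 0.1875 = 0.54 | 1.86 times |
| 10% | 1.282 | 0.175 | 0.0308 / 0.09 = 0.34 | 2.92 times |

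**4. Power at 550 children.** The share exposed (for example intubated) is not in the protocol, so 10% and 20% are assumed. The difference that gives 80% power on the score is d = (1.96 + 0.842) × √(1/n_exposed + 1/n_unexposed):

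- 10% exposed: 2.802 × √(1/55 + 1/495) = 0.40 SD
- 20% exposed: 2.802 × √(1/110 + 1/440) = 0.30 SD

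Power for the same difference after dichotomising, from the two-proportion formula with q taken as the share with problems among unexposed children:

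| Exposed | Median cut | 25% with problems | 10% with problems |
|---|---|---|---|
| 10% | 59% | 61% | 51% |
| 20% | 60% | 59% | 47% |

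A simulation of 2,000 data sets per setting compared a linear model with the Wald test of the log odds ratio. It gave 78% versus 60%, 60% and 49% at 10% exposed, and 80% versus 60%, 58% and 46% at 20% exposed.

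Over a wider assumed range (300 to 600 children, 5 to 50% exposed, the same three cuts), power falls from 80% to between 41% and 64%. The range goes down to 300 because Section 10 indicates that the planned sample size was not reached. The loss is not strictly ordered by cut-off: at 10% exposed, the median and 25% cuts perform about equally.

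**The case against.** The strongest reply is that a cut-off may exist. Section 10 defers to scoring tables that are not shown, and a SAP may define the category. The wording of 2a and 2b, which speaks of eating problems, can also be read as a yes/no clinical construct, for which logistic regression is a legitimate model. This stands in part. It means the method may be underspecified rather than invalid. A reader might infer that the cut-off will be chosen after the data are seen, but nothing in the protocol says so.

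Four other limits also stand:

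- A reader might infer that Section 10 declares these scores continuous for 2a and 2b. The explicit statement concerns the preterm-versus-term comparison and covers the BEBQ, not the CFQ. For 2a and 2b the point rests on the scale descriptions and on the test chosen between arms.
- A reader might extend the point to gestational age (2c). The logistic sentence does not name it, and Section 2 handles gestational age separately, in categories around 32 weeks.
- The protocol gives no exposure numbers, so it cannot be said that the exposed groups are small. Normality is also an assumption; the BEBQ dimensions have only 3 to 6 items each.
- Testing several scales raises multiplicity under any model. No extra inflation from a free choice of cut-off has been shown.

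None of this removes the information loss. A cut-off fixed in advance settles the arbitrariness but still discards the differences between children on the same side of it.

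**Conclusion.** The point holds in a limited form. Section 10 fixes a method for 2a and 2b that needs a binary outcome the protocol does not define, while the instruments yield scores and the arms are compared on the same sub-objective by t-test or nonparametric test. If no cut-off is supplied elsewhere, the outcome is undefined. If one is, efficiency is still about 0.64, 0.54 or 0.34 at the three cuts considered, and power falls from 80% to about 47 to 61% under the main assumptions.

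These sizes rest on roughly normal scores and on assumed shares of exposed children and of children with problems. The reach is small: exploratory, non-randomised questions within one secondary objective. The primary endpoint and the arm comparisons are unaffected. The change is worth making because the method is stated in the protocol and a better one needs no new data.

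**What to change.** In Section 10, replace logistic regression for 2a and 2b with linear regression of the child eating-behaviour scores on intubation (yes/no) and tube-feeding duration (days), adjusted for arm. Use an ordinal or rank-based model if a score is clearly skewed. Name the scores that count as child eating behaviour, since Section 8.3.7 describes the CFQ as a measure of parental beliefs, attitudes and practices.

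Keep logistic regression for outcomes that are truly binary. If a yes/no eating problem is wanted for clinical reading, report it as a supporting analysis, with the cut-off and its source stated before the scores are analysed.

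The cost is a sentence or two in Section 10. No new data, visits or questionnaires are needed.

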### 3. STUDY DESIGN

The study comprises a multicenter randomized parallel group open-label controlled intervention study in which premature born children will be randomized to receive complementary feeding at the corrected age of 12 weeks (intervention group) or at the corrected age of 17 weeks (control group). The pattern and structure of the complementary feeding will be according to the advice of the well baby clinics in the Netherlands, using a standardized nutrition schedule.

Stratification will take place according to center. In order to keep the number of subjects in the different groups closely balanced at all times block randomisation will be used. According to Altman the block size used is a multiple of the number of treatments. A blocked randomization schedule, using blocks of four, will be used. The randomisation will be computer generated by Castor edc. The research is funded by Nutricia Nederland. Nutricia Nederland will have no financial interest in this study, will not delivery food products, will not have veto in how publication of results will be. In case of any disagreement regarding publication of the data, the principal investigators ([name]) of the research will make the final decision. All data analysis will be supervised by the principal investigators.

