**Measurements for control group B (term born children)**

The term born infants will be enrolled in two hospitals, or obstetric practices and well baby clinics affiliated with the hospital, in which the preterm infants are also enrolled. The parents of the term infants will be informed with a brochure by the midwife, nurse or medical doctor during a obstetric practice visit, outpatient clinic/well baby visit or during the hospital stay/visit for the delivery. If parents give approval to the midwife or doctor, the midwife or doctor will inform the researcher or research nurse. They will contact parents by phone and provide additional information and give or send the information letter and informed consent form to the parents. Parents will be give at least one week to consider their decision after receiving the information letter and informed consent form. Informed consent will be taken by the researcher or research nurse. Treatment or follow-up of the term born child will not change depending on participation in this study. Parents will be given at least one week to consider the information before making the decision on participation. If there are no further questions, informed consent will be taken.

Parents of the term born infants are asked to:

- Fill in the BEBQ and a questionnaire regarding parental characteristics (see 8.1.3) when their child is 3 months old
- Send information to the researchers about the growth parameters (length, weight, head circumference) of their child at 3 months, 1 year and 2 years old, obtained at the well baby clinic
- Fill in four food diaries when their child is 6 months, 9 months, 12 months and 24 months old

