#### 8.1.4 Study parameters tested in controls

The control group will be the group starting with complementary feeding at the corrected age of 17 weeks. All parameters will be tested in the intervention group and in the control group.

Control group B:

- Growth parameters: Length, weight and head circumference at 3 months (with an age range of 2 weeks), and 1 year and 2 years of age (with an age range of 6 weeks).
- Other parameters (see 8.1.3)
- BEBQ (questionnaire) at 10-12 weeks of age, supplemented with questions regarding the baby feeding
- Food diaries at 6 months, 9 months, 1 year and 2 years of age, supplemented with questions about the start of complementary feeding (retrospective)

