## 8.2 Randomisation, blinding and treatment allocation

Stratification will take place according to center. In order to keep the number of subjects in the different groups closely balanced at all times block randomisation will be used. According to Altman the block size used is a multiple of the number of treatments. A blocked randomization schedule (randomly permuting blocks of four and six) at a time will be used. The randomisation will be computer generated by Castor edc. Twins will be randomized as well; the first twin will be randomized into one of the two groups, the second twin will be assigned to the same group. Patients will be randomised to introduction of complementary feeding at the corrected age of 12 weeks (intervention group) and to introduction of complementary feeding at the corrected age of 17 weeks (control group) (1:1). The allocation of the timing of the start of treatment will not be blinded.

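### Term infants come from two hospitals and preterm infants from a multicentre trial, yet the preterm–term comparison is a plain two-sample test, so hospital mix can be mistaken for an effect of prematurity

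*Protocol*

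**What the plan says.** Section 3 describes the trial of preterm infants: "The study comprises a multicenter randomized parallel group open-label controlled intervention study". Section 8.2 adds, for the randomised arms, "Stratification will take place according to center". The number of centres is not given.

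Control group B is recruited more narrowly. Section 3, under the measurements for that group, says: "The term born infants will be enrolled in two hospitals, or obstetric practices and well baby clinics affiliated with the hospital". The sentence continues "in which the preterm infants are also enrolled", so the two hospitals are among the trial's own centres.

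In section 10, "the preterm infants will be compared with the term infants to determine the difference of growth parameters, BEBQ results and food diaries", before complementary feeding starts and at 1 and 2 years. Nothing limits the preterm side to the two shared hospitals. The method follows: "For the analyses, a t-test or nonparametric test will be used".

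The next paragraph of section 10 sets out mixed models for repeated measurements and says "Infant and hospital will be added as random intercept". The group factor in those models is treatment, with the levels intervention and control. Term infants have neither level, because section 5.5 gives them no feeding intervention.

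Section 8.1.3 lists parental height, weight status, education, socio-economic status and ethnicity among the data collected, and section 8.1.4 extends that list to control group B.

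**The concern.** Sub-objectives 3 (eating behaviour by BEBQ) and 4 (growth) rest on the preterm–term contrast, which is not randomised. In the early-versus-late comparison, stratification by centre keeps the hospital mix alike in the two arms, so ignoring hospital there mainly costs precision. Here the hospital mix differs by design as soon as a third centre enrols preterm infants.

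A two-sample t-test, or its rank counterpart, treats all infants as independent and the two groups as alike except for prematurity. A difference between the catchments of the two term-recruiting hospitals and those of the other centres, for example in parental height, ethnicity or socio-economic status, would then be read as an effect of prematurity. The standard error would also leave out the between-hospital variation. The data needed for adjustment are collected in both groups, but the named test uses none of them.

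**Working it through.** **The plan's own figures.** The protocol has one sample size, for the randomised comparison. With 6% versus 13%, two-sided 5% and 80% power: n = [1.96·√(2×0.095×0.905) + 0.842·√(0.06×0.94 + 0.13×0.87)]² / 0.07² = 274.3, so 275 per group, and 550/0.95 = 579. This reproduces. It contains no term group. The only figure that bears on the preterm–term contrast is the general 5% significance level.

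**Inputs.** From the protocol: two term-recruiting hospitals that also enrol preterm infants; a multicentre preterm sample, planned at 600, a target that section 10 says was not met; no hospital term. Not in the protocol, so assumed: number of centres K, intraclass correlation ρ, number of term infants nT (50 to 300), number of preterm infants nP (300 to 600), and the share of preterm infants at the two shared hospitals.

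**Formula.** Let the outcome variance be 1 and the true preterm–term difference 0. Term infants are split equally over 2 hospitals and preterm infants equally over all K.

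- True variance of the difference: (1−ρ)(1/nT + 1/nP) + ρ(1/2 − 1/K)
- Variance the t-test assumes: 1/nT + 1/nP
- False-positive rate: 2[1 − Φ(1.96·√(assumed/true))]

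**Central case: K = 8, nP = 300, nT = 100.** Assumed variance = 1/300 + 1/100 = 0.01333. Hospital term = ρ(1/2 − 1/8) = 0.375ρ.

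| ρ | hospital part | within part | true variance | 1.96·√ratio | false-positive rate |
|---|---|---|---|---|---|
| 0.01 | 0.00375 | 0.01320 | 0.01695 | 1.74 | 8% |
| 0.02 | 0.00750 | 0.01307 | 0.02057 | 1.58 | 11% |
| 0.05 | 0.01875 | 0.01267 | 0.03142 | 1.28 | 20% |

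The square root of the hospital part is the typical size of the error that hospital mix adds to the estimate: 0.06, 0.09 and 0.14 SD of the outcome.

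**Range over the assumptions (equal preterm shares).**

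- Lowest with K of at least 3 and ρ of at least 0.01 (K = 3, 300 v 50, ρ = 0.01): 5.7%.
- Highest (K = 10, 600 v 300, ρ = 0.05): 37.8%.
- Smaller ρ (K = 10, 600 v 150): 5.5% at 0.001 and 7.8% at 0.005.
- K = 2: 4.4% to 5.0%, so no inflation.

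**Unequal preterm shares.** If a share s of preterm infants comes from the two shared hospitals and the rest is spread evenly, the factor (1/2 − 1/K) becomes (1−s)²[1/2 + 1/(K−2)]. Take K = 10, 600 v 150, where the assumed variance is 0.00833.

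- ρ = 0.01: 10.6% with equal shares (s = 0.2) and about 7% at s = 0.5. At s = 0.8 the factor is 0.025, the true variance 0.00025 + 0.00825 = 0.0085, and the rate 5.2%.
- ρ = 0.05, s = 0.8: true variance 0.00125 + 0.00792 = 0.00917, rate about 6%.

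**Simulation.** With 8,000 runs per scenario, the plain t-test agreed with the formula (K = 10, 600 v 150: 7.5%, 10.7%, 15.0% and 28.1% at ρ = 0.005, 0.01, 0.02 and 0.05). A linear model with hospital as a fixed effect gave 4.6% to 5.5% throughout. The random-intercept version was not simulated.

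**Precision cost.** With hospital as a fixed effect, only the shared hospitals inform the contrast. In the central case that is 300×2/8 = 75 preterm infants, so the standard error goes from √(1/300 + 1/100) = 0.115 to √(1/75 + 1/100) = 0.153. For K = 4 to 10 and 300 to 600 preterm against 100 term infants, the increase is 7% to 41%.

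**The case against.** The strongest reply is that the harm depends on quantities the protocol does not give. That stands. A reader might infer that the false-positive rate is well above 5%, or that every p-value and interval in sub-objectives 3 and 4 is too optimistic. The documents support neither. With two centres there is no inflation, and with most preterm infants at the shared hospitals very little.

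A second reply is that for growth the null is not what the protocol expects, since section 4.3 cites growth restraint in preterm children. That also stands against relying on the error rate alone. It does not touch the bias, which shifts the estimated difference whether or not a true one exists.

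Third, a hospital fixed effect can be less accurate than the raw contrast. In the central case the true SD of the unadjusted difference is √0.01695 = 0.130 at ρ = 0.01, against √(0.99×0.02333) = 0.152 with fixed effects. The two are equal where 0.375ρ = 0.01(1−ρ), that is ρ of about 0.026. This argues against fixed effects as the main analysis and for the random intercept the protocol already names.

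Fourth, hospital may not be the main source of difference. Term growth data come from well baby clinics, while preterm growth is measured mainly at hospital visits. No hospital term removes that. This limits what the remedy achieves.

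Finally, covariate choice is often left to an analysis plan, and this comparison is secondary. Both are true. But the protocol did not leave the method open: it named a test that does not suit the way the two groups are recruited.

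**Conclusion.** The point holds as a structural weakness of a secondary analysis. Term infants come through two hospitals, preterm infants from a multicentre trial, and the named test has no means of separating hospital from prematurity. The hospital random intercept in section 10 does not cover this contrast as written.

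If more than two centres enrol preterm infants, the estimate can be biased by hospital and catchment differences and the false-positive rate can exceed 5%. Under the assumed ICC of 0.01 to 0.05, 3 to 10 centres, 50 to 300 term infants and equal preterm shares, the rate is about 6% to 38%, and 8% to 20% in the central case. It is about 5% with two centres, and about 5% to 6% if some 80% of preterm infants come from the shared hospitals. These figures illustrate the risk under assumptions and are not estimates for this trial.

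The early-versus-late comparison, the primary endpoint and the sample size are unaffected. The change should be made but is not critical to the trial's main conclusion.

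**What to change.** In section 10, replace the two-sample test for preterm versus term with a linear mixed model for each growth parameter, BEBQ score and diary measure. It should contain a preterm/term factor, the hospital random intercept already named there (affiliated hospital for infants recruited through practices or clinics), infant sex, and the parental characteristics collected in both groups, for example height, education or socio-economic status, and ethnicity.

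Report as sensitivity analyses a model with hospital as a fixed effect, or the comparison restricted to the two shared hospitals, and the unadjusted test. The fixed-effect or restricted version matters because a random intercept is only a compromise, and its variance is poorly estimated when hospitals are few.

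State as a limitation that measurement setting differs between the groups and that a hospital term does not remove this.

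The cost is a sentence or two of text. No recruitment or procedure changes, and the parental data are already collected. The standard error will be somewhat larger than the t-test reports. In the central case the fixed-effect version is about a third larger (0.153 against 0.115), but the smaller figure is not a valid standard error when hospitals differ.

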#### 8.1.3 Other study parameters (if applicable)

Other study parameters are age, gender, height, weight status, family history, allergy/atopy status, education, social economic status, and ethnicity of the parents. Maternal information regarding the pregnancy, parity and delivery are collected as well, including maternal illness during pregnancy, such as maternal diabetes mellitus, hypertensive disorders during pregnancy, and thyroid disease. This parameters will be obtained via digital questionnaires or child records. Information on perinatal and early life factors, such as APGAR-score, birth weight, reason for prematurity, respiratory support, blood transfusion, antibiotics use, NICU admission, type of feeding until complementary feeding is started, and illness are prospectively collected. Furthermore, information on sickness and medical check-ups.

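### The non-randomised preterm versus term comparison is planned only as an unadjusted test, although parental covariates that could be adjusted for are collected in both groups

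*Protocol*

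**What the plan says.** Sub-objective 3 (section 2) is "to determine if term born infants (control group B) have less eating problems in comparison to preterm infants before the start of complementary feeding", measured by the BEBQ. Sub-objective 4 compares growth parameters of preterm and term infants before solids and at 1 and 2 years.

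The analysis is in section 10: "For control group B, the preterm infants will be compared with the term infants to determine the difference of growth parameters". The same comparison is planned there for the BEBQ and the diaries. The method follows in the same paragraph: "For the analyses, a t-test or nonparametric test will be used". Adjustment, matching and stratification are not mentioned for this contrast.

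On recruitment, section 3 says: "The term born infants will be enrolled in two hospitals, or obstetric practices and well baby clinics affiliated with the hospital". These are places where preterm infants are enrolled too, but the preterm sample itself comes from a multicentre trial.

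On data, section 8.1.3 lists age and gender, and then "height, weight status, family history, allergy/atopy status, education, social economic status, and ethnicity of the parents". Section 3 asks parents in group B to "Fill in the BEBQ and a questionnaire regarding parental characteristics (see 8.1.3) when their child is 3 months old", and section 8.1.4 again lists the parameters of 8.1.3 for group B.

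**The concern.** Randomisation balances the early and late arms. It does nothing for preterm against term, where two separately recruited samples of families are compared. Parental size, education, social economic status and ethnicity can bear on a child's growth and on how parents report feeding. If the two samples differ on these, the unadjusted difference contains that family contrast as well as whatever goes with gestational age. A t-test or rank test cannot separate the two, and a larger sample does not shrink the bias.

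What is at stake is how sub-objectives 3 and 4 and the group B diary comparison can be read. The information needed to examine the question is already collected, but the named analysis cannot use it.

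**Working it through.** **1. Is the contrast adjusted anywhere else in the protocol?**

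- *Eligibility (section 4.2).* Group B has the same clinical exclusions as the preterm infants. This aligns disease status and balances no family characteristic.
- *Dutch growth curves (section 10).* These place each child against a national reference and do not remove differences between families.
- *Mixed model (section 10, after the group B paragraph).* Its fixed factors are treatment (intervention, control), time and their interaction, with random intercepts for infant and hospital. It has no preterm/term factor and no parental covariate, and group B infants belong to neither treatment level.
- *Imputation (section 10).* This fills in missing values and adjusts nothing.

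So nothing in the protocol adjusts this comparison.

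**2. Are the covariates available in both groups?** Yes, by sections 3, 8.1.3 and 8.1.4. The sentence in 8.1.3 runs child and parental items together. I read age and gender as the child's, and the items from height onwards as the parents'. The group B text supports this, since it calls the instrument a questionnaire on parental characteristics. If height and weight status were meant for the child, education, social economic status and ethnicity would still be parental.

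**3. How large could the bias be?** The plan states no figure to reproduce. Let D be the preterm-term gap in one parental factor, in SD, and r its correlation with the child outcome. In outcome SD units:

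unadjusted difference = true difference + r × D

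Both inputs are assumed, with D from 0.2 to 0.5 and r from 0.2 to 0.4:

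| D | r | Bias (SD) |
|---|---|---|
| 0.2 | 0.2 | 0.04 |
| 0.3 | 0.3 | 0.09 |
| 0.5 | 0.4 | 0.20 |

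**4. How does that compare with sampling error?** The size of group B is not stated, so this is illustration only. Take 550 preterm infants (2 × 275, section 4.3) and an assumed 200 term infants:

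SE = √(1/550 + 1/200) = 0.083 SD

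With r = 0.2 and D = 0.3 the bias is 0.06 SD, and 0.06/0.083 = 0.73 standard errors. If the true difference were zero, a two-sided 5% test would reject with probability Φ(−1.96 + 0.73) + Φ(−1.96 − 0.73) = about 11%. A simulation of 3,000 trials gave 12% unadjusted. With the factor in a linear model it gave 4.7%, and the mean estimate returned to about zero. That is the best case for adjustment, because the only family difference simulated was a measured one. Section 10 says the planned sample was not reached, so the real standard error would be larger and this rate lower, but the bias would not change.

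**The case against.** The strongest reply is that the protocol sets out to describe a difference. A reader might infer that family differences will be reported as an effect of prematurity, and that the p-values and intervals are therefore wrong. The documents do not support that. Sections 2 and 10 speak of a difference and of a comparison, and keep the language of effect for early against late introduction. For the plain difference between the two populations sampled, an unadjusted test addresses the stated quantity. This part of the reply stands. What remains is that the reported difference mixes sources which the collected data could help to separate.

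A reader might also infer that group B are self-selected volunteers while the preterm families are not. Section 11.2 shows otherwise: both sets of parents receive a brochure and consent voluntarily. The sites overlap as well. No passage shows that the families differ in any particular way.

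The size rests wholly on assumptions. A false-positive rate also presupposes a true difference of zero, which fits growth poorly because section 4.3 itself cites growth restraint in preterm infants. For growth the bias in SD units is the figure to use, and over much of the assumed range it is small.

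Finally, covariate sets are often left to a statistical analysis plan, which is not at hand. That lowers the weight of the point. It does not remove it, because the protocol names the test and does not leave the method open.

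**Conclusion.** The point holds as a minor one. For a non-randomised comparison the protocol names only an unadjusted test, while collecting parental covariates in both groups that this test cannot use. Any family differences between the samples go into the reported preterm-term difference. Their size and direction are unknown from the documents. Under assumed gaps of 0.2 to 0.5 SD and correlations of 0.2 to 0.4, the bias is 0.04 to 0.20 SD.

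The reach is limited to sub-objectives 3 and 4 and the group B diaries. The comparison of early with late introduction, including the primary endpoint, is not touched.

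**What to change.** In section 10, keep the unadjusted preterm-term difference as the descriptive result. Beside it, report an adjusted difference with its 95% interval from a regression containing a preterm/term factor, child sex and a set of the 8.1.3 parental covariates named in advance: parental height, weight status, education, social economic status and ethnicity. For outcomes measured at several visits, use a mixed model with the same terms. Allow for twins, since section 8.2 places both in the same arm and their outcomes and parental data are not independent.

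State the rule for choosing covariates. Leave out consequences of preterm birth, such as NICU care and milk type, and pregnancy complications on the pathway to preterm birth. A ban on every possible cause of preterm birth would be too broad, because some of the parental factors to be adjusted for may themselves be related to it.

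The cost is a short addition to the text and some analysis work, with no new data collection. Some questionnaire items will be missing, and the multiple imputation already planned in section 10 can cover them. Adjustment deals only with measured factors, so the report should say that unmeasured family differences may remain.
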